### Inclusion and exclusion criteria

Patients aged 18 and over who turn to their GP for help with insomnia complaints are evaluated for eligibility. Inclusion criteria are assessed using a screening questionnaire (t0) and include: difficulty initiating or maintaining sleep for at least 30 minutes a night, for at least three nights a week, for at least three months, causing clinically significant distress and/or impairment in daily functioning, i.e. meeting criteria for a DSM-5 diagnosis of insomnia [1]. Exclusion criteria are: no access to the internet, inadequate proficiency in Dutch, meeting criteria of the diagnosis of sleep apnea (assessed by the GP and in the screening questionnaire using the Screening for Sleeping disorders [46], pregnancy or breast feeding during the trial, working in night shifts, psychological treatment in the last six months, being suicidal (assessed using 5 items from the MINI diagnostic interview [47]), and schizophrenia or psychotic disorder (“Have you been diagnosed with schizophrenia or psychosis?”, to which participants reply ‘Yes’ or ‘No’). Other comorbid psychological disorders and somatic diseases are allowed. The use of (sleep) medication is also allowed and tracked.

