### Primary outcome: insomnia severity

The primary outcome of the study will be insomnia severity as measured by the Insomnia Severity Index [49]. The ISI consists of 7 items scored on a 5-point Likert scale (0 = not at all, 4 = extremely) and scores range from 0–28, higher scores indicating more severe insomnia. The ISI assesses the nature, severity and the impact of insomnia. Previous research has indicated that the Insomnia Severity Index (ISI) is a valid and reliable instrument to quantify perceived insomnia severity and presents a clinically useful tool in screening as well as outcome measurement. It possesses adequate internal consistency (Cronbach’s alpha = .90), is sensitive to changes in perceived sleep difficulties over time [50] and has been validated for online use [51]. We use a community sample cut-off score of ≥10 to define clinical insomnia [50].

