### Statistical analysis

The study will be conducted in adherence to the Consolidated Standards of Reporting Trials (CONSORT; [65]) statement. For all analyses statistical significance will be set at *p* < .05. In accordance with the intention-to-treat principle, we will use all data independent of treatment or study completion. Missing values will be imputed using multiple imputation for calculation of Cohen’s *d* [66, 67].

Between group interaction effects (time × group) will be tested with Generalized Estimating Equations (GEE). Variables that are not distributed equally or that predict dropout will be added to the model as covariates. This technique is suitable for the analysis of the longitudinal relationship between a continuous outcome variable and several time-dependent and time independent covariates [68].

We will describe the magnitude of the effect (effect size) with Cohen’s *d*. We will calculate this by dividing the difference in scores of the two groups at post-test by the pooled standard deviation of change scores (Cohen’s *d*). This can thus be interpreted as the number of standard deviations the intervention group scores better than the control group [69].

Next, we will compare the intervention and control group with regard to the percentage of patients who have (1) improved and (2) recovered. An ISI score of 10 or lower will be considered recovery. Improvement will be defined as an ISI change score of 7 points or more [50]. This information will be used to calculate the relative risk and the number needed to treat [70].

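### The cut-offs for clinical insomnia (ISI ≥10) and recovery (ISI ≤10) overlap at a score of 10, which shifts the recovery percentages and the recovery-based relative risk and NNT

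*Protocol article*

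**What the plan says.** All references are to the protocol article.

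- **Primary outcome: insomnia severity.** The ISI has seven items, each scored 0 to 4; "scores range from 0–28, higher scores indicating more severe insomnia". The case definition follows: "We use a community sample cut-off score of ≥10 to define clinical insomnia".
- **Statistical analysis.** The arms are compared on the percentages improved and recovered. For recovery: "An ISI score of 10 or lower will be considered recovery". Improvement is a separate criterion, an ISI change of at least 7 points. Both outcomes feed the relative risk and the number needed to treat. The section also commits to intention-to-treat, using all data whether or not patients complete treatment or the study.
- **Inclusion and exclusion criteria.** Entry is by symptom duration and frequency, "difficulty initiating or maintaining sleep for at least 30 minutes a night, for at least three nights a week, for at least three months", plus distress or impairment. No ISI threshold is listed.
- **Strengths and weaknesses.** The ISI is described as adding information on severity. It is not described as a condition of entry.

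**The concern.** A case threshold and a recovery threshold on the same instrument should split the scale without overlap. Here both include the value 10. A patient who ends at 10 is reported as recovered while still meeting the trial's own definition of clinical insomnia.

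A second, weaker issue follows from the entry criteria. Recovery is defined by the end score alone and no baseline ISI is required. A patient who enters at 8 and stays at 8 therefore counts as recovered without having changed.

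At stake are the recovery percentages and the RR and NNT built on them, which are figures that clinicians tend to quote. If the overlap stays unresolved, the choice between ≤10 and <10 could also be made after the results are known.

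**Working it through.** **1. The plan's own figure.** The only design figure that can be reproduced is the sample size. With d = 0.50, 80% power and alpha 0.05 (two-sided assumed), the t-test calculation gives 63.77, so 64 per arm. With 20% dropout, 64 / (1 − 0.20) = 80 per arm, or 160 in total. This agrees with the article and does not depend on any ISI cut-off. The article states no expected recovery rate, RR or NNT.

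**2. The overlap.** On integers from 0 to 28, the set ISI ≥10 and the set ISI ≤10 share exactly one value, 10.

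**3. Size of the effect at post-treatment.** The article gives no ISI mean or SD, so these inputs are assumptions: a normal distribution rounded to whole scores, SD 5, and a mean difference of 0.5 × 5 = 2.5. The formulas are:

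- P(ISI ≤10) = Φ((10.5 − mean) / SD)
- P(ISI ≤9) = Φ((9.5 − mean) / SD)
- RR = p_int / p_ctl
- NNT = 1 / (p_int − p_ctl)

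For means of 10 (intervention) and 12.5 (control):

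- Recovery as ≤10: Φ(0.1) = 54.0% and Φ(−0.4) = 34.5%. RR = 0.540 / 0.345 = 1.57; NNT = 1 / 0.195 = 5.1.
- Recovery as <10: Φ(−0.1) = 46.0% and Φ(−0.6) = 27.4%. RR = 0.460 / 0.274 = 1.68; NNT = 1 / 0.186 = 5.4.
- Share scoring exactly 10, from unrounded values: 8.0% and 7.0%, or about 6 of 80 patients per arm.

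| Means (int v ctl), SD 5 | Rule | Recovery | RR | NNT |
|---|---|---|---|---|
| 10 v 12.5 | ≤10 | 54.0% v 34.5% | 1.57 | 5.1 |
| 10 v 12.5 | <10 | 46.0% v 27.4% | 1.68 | 5.4 |
| 12 v 14.5 | ≤10 | 38.2% v 21.2% | 1.80 | 5.9 |
| 12 v 14.5 | <10 | 30.9% v 15.9% | 1.94 | 6.7 |

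Over a wider grid (control mean 12 to 15, SD 4 to 6, d = 0.5), about 5 to 9% of control and 6 to 10% of intervention patients score exactly 10. RR runs from 1.49 to 2.04 with ≤10 and from 1.58 to 2.26 with <10. NNT runs from 5.1 to 7.4 and from 5.1 to 9.4.

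**4. Patients already at or below 10 at entry.** With an assumed baseline mean of 15 to 18 and SD of 3.5 to 4.5, 1.6 to 15.9% would enter at ISI ≤10. To see what this does, let a fraction f in each arm start there and count as recovered, and let true recovery among the rest be 30% v 50% (assumed). The observed rate is then f + (1 − f) × p.

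| f | Control | Intervention | RR | NNT |
|---|---|---|---|---|
| 0 | 30.0% | 50.0% | 1.67 | 5.0 |
| 2% | 31.4% | 51.0% | 1.62 | 5.1 |
| 5% | 33.5% | 52.5% | 1.57 | 5.3 |
| 10% | 37.0% | 55.0% | 1.49 | 5.6 |

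Recovery rises in both arms and the contrast between them shrinks.

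**The case against.** The strongest reply is that the recovery rule is unambiguous taken alone. ISI ≤10 can be computed and is applied identically to both randomised arms. The ≥10 cut-off is not used for eligibility or in any analysis that the article describes, so the conflict could be called a matter of labelling at one score. Much of this stands. A reader might infer from the overlap that the recovery rates, RR and NNT are invalid. The documents do not support that: the randomised comparison remains valid, and the consequence is misclassification at a single score.

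Nor does the overlap consistently flatter the intervention. In the scenarios in the first table, ≤10 gives the weaker RR and the slightly better NNT.

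On the missing baseline condition, an end-state definition of recovery is legitimate under randomisation. Details of this kind are often left to a full protocol or analysis plan that is not shown. The share entering at ≤10 is also unknown. The required symptoms and impairment probably thin the lower tail, so the percentages above may be too high. A further inference, that patients below the cut-off at entry bias the result towards i-Sleep, is not supported either, because the calculation shows dilution. Restricting the main analysis to baseline cases would also depart from the stated use of all data under intention-to-treat.

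The contradiction itself survives. The article states two incompatible thresholds for its primary instrument, and no separate document is needed to see it.

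**Conclusion.** The point holds in a limited form. The case and recovery definitions both include ISI = 10 and must be reconciled. The effect is confined to the recovery percentage and the RR and NNT based on it. With SD 5, d = 0.5 and means of 10 and 12.5, 7 to 8% of patients per arm are affected, RR moves from 1.57 to 1.68 and NNT from 5.1 to 5.4. These sizes rest wholly on assumed means, SDs and a rounded normal shape. The overlap itself rests on no assumption.

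Improvement (a change of 7 points or more) does not use the cut-off of 10, so its RR and NNT are untouched. The GEE analysis of continuous ISI, Cohen's d and the sample size of 160 are also unaffected.

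The article does not show which boundary was intended. The recovery sentence carries no citation of its own, and the source cited for the case cut-off is not at hand. The absence of a baseline ISI floor is real, but it supports a supplementary analysis and not a change to the main one. Severity: minor to moderate.

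**What to change.** Before outcome data are seen, make the two cut-offs mutually exclusive:

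1. Most directly, define recovery as ISI <10, the complement of the plan's own case definition. If ≤10 is the intended recovery rule, restate the case definition as ISI >10 instead.
2. Use the chosen rule for the recovery percentage and for the recovery-based RR and NNT.
3. Keep all randomised patients in the main recovery analysis. Add a supplementary analysis of recovery among patients who met the reconciled case definition at baseline, with the same rule in both arms. That set is fixed before randomisation, so the comparison within it stays randomised. The cut-offs must be reconciled first: a baseline condition of ≥10 combined with recovery at ≤10 would still admit patients who meet the recovery rule on entry.

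The cost is two or three sentences and one extra table row. With <10, the recovery percentages become somewhat lower, by 7 to 8 percentage points per arm in the main example. With the case definition restated as >10, they do not change. The sample size stays at 160. Under Trial status the article reports that the first participants are being recruited, so at that stage the change could precede any outcome data.

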### Cost-effectiveness and cost-utility analysis

Both cost-effectiveness and cost-utility analyses will be performed. Cost-effectiveness analysis entails measuring the value of the new therapy i-Sleep by calculating the difference in costs between i-Sleep and care-as-usual, and dividing this by the difference in effectiveness of both treatment options (i.e., calculating the cost-effectiveness ratio) [71, 72].

The cost-utility analysis represents the costs associated with gaining one quality-adjusted life year (QALY). Missing cost and effect data will be imputed using multiple imputation. Seemingly unrelated regression will be used to estimate cost and effect differences while adjusting for potential confounders. We will use bootstrapping to estimate uncertainty surrounding the cost-effectiveness estimates to account for the skewed distribution of costs. Cost-effectiveness planes and cost-effectiveness acceptability curves will be estimated to show statistical uncertainty surrounding the cost-effectiveness estimates.

### Budget impact analysis (BIA)

A budget impact analysis (BIA) is used to calculate expected changes in the expenses if the new intervention i-Sleep is adapted into the healthcare system. For the BIA the population of people with insomnia will be estimated using Dutch epidemiological data. We will extrapolate the effectiveness of the treatments using a Markov model based on the estimates obtained from the proposed study. We will evaluate different implementation scenarios (0 %, 50 %, 100 %, subgroups only). Aggregated and disaggregated (e.g. GP/PWP care, secondary care, and productivity losses) total costs per year will be presented for the different perspectives and scenarios. We expect that the intervention will lead to increased work productivity in comparison to care-as-usual, and that the largest economic benefits generated by the intervention are related to reduced productivity losses. Costs associated with the treatment condition are costs of the use of the intervention platform, and invested time of the PWPs.

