### Aims and hypotheses

At the moment G.P. care for insomnia is mainly consisting of sleep hygiene and prescribing medication and, therefore, is often suboptimal, i.e. not adhering to guidelines. The objective of this pragmatic trial is to evaluate the effectiveness and cost-effectiveness of an online CBT-I intervention, i-Sleep, for patients with insomnia in comparison with care-as-usual. Patients will receive online coaching by PWPs working in general practices. We expect the intervention to improve the quality of care for insomnia (i.e., lead to higher improvement rates because more people receive care according to the guideline) and to be cost-effective compared to care-as-usual because of low intervention costs, less healthcare utilization and less lost productivity. We expect that patients in the intervention group will show a reduction in insomnia complaints and improved sleep parameters, suffer fewer daytime consequences, and have lower costs related to healthcare utilization and lost productivity than patients in the care-as-usual group.

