## Methods/design

### Study design

This study is a pragmatic randomized controlled trial with an economic evaluation from a societal perspective alongside. Patients referring to their GP with insomnia are randomized to either the online intervention group, who will gain access to the guided online intervention, or the control group, who will receive G.P. care-as-usual and will be offered the investigated guided online intervention six months after inclusion. The study protocol, information brochure, questionnaires, recruitment material and informed consent form were approved by the Medical Ethics Committee of the VU University Medical Centre (METC VUmc, registration number 2015/258). The trial is registered with the Netherlands Trial Register (NTR 5202).

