Patients in the intervention condition will receive guidance from a psychological wellbeing practitioner (PWP) in each general practice, usually a (psychiatric) nurse. We will provide training for the PWP in CBT-I as well as in providing online feedback. The training will consists of a 1.5 hour workshop, guided practice with the online course and feedback training. PWPs will be supervised by the first author (TZ) and an experienced CBT psychologist. Patients in both conditions are also allowed to receive care-as-usual from their GP or the PWP.

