### Cost measures

Healthcare utilization will be assessed in two ways. First we will use data derived from GP records. We will assess the number of consultations with GPs, and general well-being practitioners as well as medication prescriptions. Next, we will ask the patients themselves which other healthcare services they used (GP and other) and which sleep and other medication they took. For this we will use the TiC-P [62] (Hakkaart-van Roijen et al., 2002). The Short Form Health and Labour Questionnaire which is also part of the TiC-P will be used to measure absenteeism from paid and unpaid work, and presentism [62]. Healthcare utilization will be valued using Dutch standard tariffs [63]. Costs associated with lost productivity will be estimated according to the friction cost approach [64].

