There are also potential weaknesses in our study. First of all, it might be a weakness that our intervention lacks any face-to-face contact. We might also have chosen to offer the treatment in blended format where patients receive a combination of online and face-to-face therapy. Blended care might be more acceptable to the patient as well as the professionals and it has been suggested to be effective in other disorders, e.g. depression [74]. However, for this trial we chose not to blend care, because a purely online treatment was deemed more feasible, more cost-effective and easier to implement. A second potential weakness is that we include a convenience sample of GPs. The participating GPs might be more interested in insomnia than those who do not participate. This means that care-as-usual might be of higher quality than provided on average. Also, the participating GPs offer access to a mostly urban population. A third potential weakness is that we include professionals (PWPs) who are currently employed by GPs but who have varying levels of expertise in insomnia and online treatments. Even though we will train the PWPs, and we will supervise them during the trial, it may lead to heterogeneity in the way treatments are delivered. In other words, the high external validity may lead to less internal validity.

Another potential limitation is the fact that we do not establish the DSM diagnosis based on clinical interviews. Patients are referred to us by the GP who establishes clinically relevant sleep problems. The sleep diary, actigraphy and ISI provide us with further information about the severity of the insomnia. Using online questionnaires eliminates the risk of interviewer bias and it ensures relatively easy follow-up measurements while minimizing the burden for participants.

Also, it may be a disadvantage that participants do not gain access to the online treatment immediately: the trial involves a series of practical steps and registration that take some time between enrollment and actual participation. This may influence patients’ motivation negatively.

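### The stated cost of i-Sleep covers platform use and PWP time but not the trainer and supervisor time that the trial provides, so applied as written it understates the intervention cost by an unknown, possibly small, amount

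*Protocol article*

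**What the plan says.** The only list of intervention costs in the protocol article closes the section Budget impact analysis (BIA): "Costs associated with the treatment condition are costs of the use of the intervention platform, and invested time of the PWPs".

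The section on the intervention describes what goes into delivery. The trial team trains the practitioners: "We will provide training for the PWP in CBT-I as well as in providing online feedback". On content: "The training will consists of a 1.5 hour workshop, guided practice with the online course and feedback training". The same paragraph has the PWPs supervised by a trial author and by an experienced CBT psychologist. Strengths and weaknesses repeats both elements, as measures taken against uneven delivery: "Even though we will train the PWPs, and we will supervise them during the trial".

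On the economic evaluation, Study design sets the perspective: "This study is a pragmatic randomized controlled trial with an economic evaluation from a societal perspective alongside". Cost measures covers healthcare use and lost productivity ("Healthcare utilization will be valued using Dutch standard tariffs") and has no item for the intervention itself. Cost-effectiveness and cost-utility analysis describes the ratio as "calculating the difference in costs between i-Sleep and care-as-usual, and dividing this by the difference in effectiveness of both treatment options", again without saying what the intervention cost contains.

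**The concern.** The budget impact sentence is worded as a statement of what the costs are. It carries no wording that marks it as a set of examples, although the same section uses such wording for its cost breakdown two sentences earlier. The time of a workshop trainer or a supervising psychologist is neither platform use nor PWP time. The list therefore leaves out resources that the article itself makes part of delivery.

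The effect in the trial will be obtained with trained and supervised PWPs. Valuing that effect without the inputs behind it lowers the cost set against it. Under a societal perspective such inputs count whoever pays for them. The omission also touches a stated hypothesis, since Aims and hypotheses expects i-Sleep to be cost-effective partly "because of low intervention costs, less healthcare utilization and less lost productivity". In the budget impact analysis, the 50 % and 100 % implementation scenarios would need more PWPs to be trained, and that outlay would not appear.

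**Working it through.** **1. Match the inputs to the list.**

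| Delivery input in the article | Platform use? | PWP time? |
|---|---|---|
| PWP coaching of patients | no | yes |
| PWP hours spent in training | no | arguably yes |
| Trainer hours | no | no |
| Supervisor hours (trial author, CBT psychologist) | no | no |

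The certain omission is the last two rows. PWP hours in training can be read as already covered.

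**2. Direction.** Let c ≥ 0 be the omitted cost per i-Sleep patient. The cost difference used is ΔC − c instead of ΔC. For a value λ per unit of effect, the net benefit λΔE − ΔC becomes λΔE − ΔC + c. It rises by c at every λ, so the acceptability curve moves towards i-Sleep or stays where it is.

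**3. The denominator.** The article states no intervention cost to reproduce. The figure that bears on cost per patient is the arm size of 80 (section Sample size).
- Normal approximation, d = 0.50, power 80 %, two-sided alpha 0.05: 63 per arm; 63/0.8 = 78.75, rounded up to 79.
- t-test: 64 per arm; 64/0.8 = 80.

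The stated 80 per arm reproduces.

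**4. Illustration of size.** Formula: hours per patient = (1.5 × number of workshops + supervisor hours) / patients; cost = hours × rate. From the article: 1.5 h per workshop and 80 patients. Assumed: 1 to 15 workshops, 10 to 150 supervisor hours in total, EUR 50 to 100 per hour. Trainer time for guided practice and feedback training is left out, because no hours are given for it.
- Low: (1.5 × 1 + 10)/80 = 11.5/80 = 0.14 h; × EUR 50 = about EUR 7.
- High: (1.5 × 15 + 150)/80 = 172.5/80 = 2.16 h; × EUR 100 = about EUR 216.
- Over 160 patients, if all controls also take up guided i-Sleep after six months: 11.5/160 = 0.07 h, about EUR 4; 172.5/160 = 1.08 h, about EUR 108.

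These figures show how wide the range is. They do not estimate the omission.

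**The case against.** Several objections carry weight.

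- **The sentence stands in the budget impact section.** A reader might infer that the cost-effectiveness and cost-utility results are certain to be biased. The article does not say so: neither Cost measures nor the cost-effectiveness section adopts the list. Carrying it over is a reasonable inference, because no other definition is given and the sentence speaks of the treatment condition, but it remains an inference.
- **The size may be small.** A reader might also size the omission by PWP training hours set against coaching hours. That does not work. Those hours may already count as PWP time, and coaching time is the wrong yardstick. The relevant quantity is the full societal cost difference, which includes productivity losses, where the article expects the largest benefits.
- **Training is a start-up cost.** It is spread over each PWP's later caseload, so cost per patient falls at roll-out. Controls are offered i-Sleep after six months, which widens the base further. In a comparison that runs beyond that point, part of the omitted cost would also belong to the control arm.
- **Some supervision may be research-only.** It is given partly by a trial author and is described as taking place during the trial. The article does not say whether it would continue in routine care. Including only what would be implemented is defensible if it is stated.
- **An article condenses.** Unit prices and amortisation may well stand in the full protocol. That excuses missing detail. It does not remove the mismatch between a sentence saying what the costs are and a delivery model that contains more.

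The first four objections limit scope and size. None shows that trainer and supervisor time is covered.

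**Conclusion.** The point holds in a limited form. As written, the list leaves out trainer and supervisor time that the article makes part of delivering i-Sleep. This understates i-Sleep costs in the budget impact analysis, and in the cost-effectiveness and cost-utility analyses if they use the same definition. The direction favours i-Sleep.

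The size cannot be computed from the article. Under the assumptions above it runs from a few euros to about EUR 216 per patient, and it could be negligible against the societal cost difference. A stronger reading, that a material bias in the cost-effectiveness results is established, is not supported. The primary effectiveness analysis is not affected. The point is still worth correcting, because the error would run in one known direction on an economic claim that rests partly on low intervention cost.

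**What to change.** - Log trainer and supervisor hours, and PWP hours in training, from now on. Trial status says that the first participants are being recruited, so this is still feasible, and the hours would be hard to reconstruct later.
- Define the intervention cost as platform use, PWP time, trainer time and delivery-related supervision time, and state that PWP training hours count as PWP time.
- Spread training costs over the expected caseload per PWP.
- State that this one definition applies to the cost-effectiveness, cost-utility and budget impact analyses.
- If part of the supervision is judged research-only, say which part and why, and report a sensitivity analysis with and without it.

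The cost is a little logging work, a few sentences in the analysis plan, and a slightly less favourable cost-effectiveness ratio for i-Sleep.
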